## **5.4 Cognitive Task Administration**

Wechsler Test of Adult Reading (WTAR): (Harcourt assessment, 2001) The WTAR is a standardized test of reading that requires subjects to read a list of words aloud as best as they can. The WTAR is highly correlated with overall intellectual abilities and provides a quick measure of intellectual functioning, especially pre-morbid functioning in the case of patients. The WTAR takes approximately 5 minutes to administer.

Screen of Cognitive Impairment in Psychiatry (SCIP): : used to estimate cognitive function in individuals with psychiatric illness. This assessment is a valid and reliable tool (Purdon, 2005) and takes 10-15 minutes to administer.

Belief Against Disconfirmatory Evidence (BADE) Task: You will be presented with a series of statements about different fictional individuals. You will then rate the plausibility of four explanations for each scenario. This task takes approximately 20-30 minutes.

3-Probabilistic Reversal Learning Task: In this task, we will show you three decks of cards on the computer screen. Each deck will have a hidden probability of reward. Using the keyboard, you will select the deck of cards you think will earn you the greatest number of points. You will then receive feedback about the reward outcome for the deck you selected (+100 or -50 points). You are instructed to find the best deck, that will earn you the most points. However the best deck may change throughout the experiment. This task takes approximately 15-30 minutes to complete.

Levels of Emotional Awareness Test (eLEAS): In this task, participants will be read up to 20 scenarios describing social interactions. After each scenario they will be asked two follow-up questions about how the scenario may make someone feel. This task takes approximately 15 to 30 minutes.

Horizon Task: In this task, participants will choose between two slot machines, like what you might find in a casino. Each machine will reward them in points, between 1 and 100. Participants may stick with the same machine or switch between them. The goal is to earn as many points as possible. This task takes approximately 12-15 minutes.

Emotional Stroop - Participants will observe neutral and negative words that are presented in different colors. They will be asked to state the color the word is printed in. This task takes approximately 15-20 minutes to complete.

Attentional Blink Task - Participants will observe a series of neutral images and asked to identify when they see a specific target image by pressing a button. Sometimes, a more threatening image will appear on the screen, however their task will not change. This task will take 15-20 minutes.

Anticipating Future Outcomes - Participants will be presented with different possible future events (e.g. having an argument with a friend) and will be asked to rate how likely that is to occur and how bad it would be for them if it did occur. This task will take about 10 minutes.

Clinical Assessments Diagnostic Interview (Visit 1) You may be asked to complete an interview about psychiatric symptoms you currently have or have experienced in the past. These will include questions about

your mood, anxiety, substance use, psychosis, and any compulsive behaviors. You will be asked about when these experiences happened and how they impacted your daily life. This interview is expected to take 1-3 hours and you will be offered breaks as needed.

### **5.5 Self-Report**

**Self Esteem Scale:** is a 40 item self-reported questionnaire designed to measure the self and perceived self-esteem. The Self Esteem Scale takes approximately 5 minutes to complete.

**Baer Grant Defeatist Beliefs Scale:** (Grant & Beck 2008) is a 5 item self-report questionnaire designed to measure one's defeatist beliefs about themselves. This scale should take less than 5 minutes to complete

**Baer Grant Asocial Beliefs Scale:** (Grant & Beck 2010) is a 7 item yes-no self-report questionnaire asking about one's interaction with others. This scale should take less than 5 minutes to complete.

**Beck Depression Inventory-II :** (BDI-II, Beck et. al. 1996) is a 21-item self-reported questionnaire designed to measure the severity of depression in adolescents and adults and addresses all nine of the diagnostic criteria for a major depressive episode that are listed in the DSM-IV-TR. The BDI-II takes approximately 5-10 minutes to complete.

**Penn State Worry Questionnaire:** The PSWQ is a widely used measure of worry severity. It assesses worry through a 16-item self-report scale using a Likert Scale. The PSWQ take approximately 5 minutes to complete.

**Dunn Worry Questionnaire:** The Dunn Worry Questionnaire is a 15-question self-reported measure of worry over the past month using a Likert Scale. Worry questions focus on general worry as well as worry about others trying to upset or harm you. The DWQ takes approximately 5 minutes to complete.

**Perseverative Thinking Questionnaire:** This 15-question self-report assesses perseverative thinking style on a Likert Scale. The PTQ takes approximately 5 minutes to complete.

**Warwick-Edinburgh Mental Wellbeing Scale (WEMWBS):** (Brown et. al. 2007) is a 14 item self-report scale that covers both feeling and functioning aspects of mental wellbeing like resilience and protective factors. The WEMWBS is used in multiple geographical locations, languages, and cultural contexts with extensive validity. The WEMWBS takes approximately 5 minutes to complete.

**Choice of Outcome in CBT for Psychosis (CHOICE):** (Greenwood et. al. 2009) is a 24 item self-report scale that provides scores for the severity and the satisfaction of an individuals intervention with a range of difficulties. The measure has good test-retest reliability, face and construct validity, and sensitivity to change. The CHOICE takes approximately 5-10 minutes to complete.

**Beck Cognitive Insight Scale:** (BCIS; Beck et al. 2004) is a 15-item self-report questionnaire designed to evaluate patients' self-reflectiveness and their overconfidence in their interpretations of their experiences. The scale demonstrates good convergent, discriminant, and construct validity. The BCIS takes approximately 5 minutes to complete.

**Difficulties in Emotion Regulation (DERS-16):** This 16-item self-report assesses one's ability to regulate emotions when upset. It takes approximately 5 minutes to complete.

**The Sleep Conditions Indicator (SCI)** is an 8-item assessment of sleep quality and behaviors. It should take about 3

**Working Alliance Inventory (WAI)** is a 12-item questionnaire about how an individual feels about their therapist/counselor

Credibility/Expectancy Questionnaire is a 6-item questionnaire about expectations and perceived credibility of a therapy intervention.

Revised 28-Item Racial and Ethnic Microaggression Scale (R28REMS; Forrest-Bank et al., 2015): This revised version of Nadal (2011)'s 45 item Racial and Ethnic Microaggression scale includes 28 items assessing frequencies of covert discrimination events. This measure takes about 10 minutes to complete.

General Ethnic Discrimination Scale (GED; Landrine et al., 2006): an 18-item measure of perceived ethnic discrimination. This takes about 5-10 minutes to complete.

**5.6 MRI Procedures (Baseline and Week 8):** MRI scans of the brain will be obtained using the MRI scanners in the Center for Human Studies in the Vanderbilt University Institute for Imaging Science (VUIIS), located in the Vanderbilt Hospital and Medical Center North. This will require approximately 60-90 minutes and no contrast agent will be used. Participants may be invited to complete multiple MRI sessions as part of the study.

**5.6.a MRI Screening:** The participant will fill out the MRI Procedure Screening Form. The purpose of this form is to ensure that there are no implanted medical devices or metals that could injure the subject if exposed to a high magnetic field. This form will be filled out in a private room adjacent to the MRI scanner and reviewed by the MR Technologist and the research assistant.

**5.6.b Scanning Procedures:** Imaging studies will take place on a Phillips 3.0 T MRI scanner. The magnet and the magnet's control console are in separate rooms, but the investigator and the subject will be in voice communication at all times, and the investigator will be able to see the subject through a window. All data acquired on the scanner will be securely transferred over the Vanderbilt network to the Institute of Imaging Science's server. Imaging data will be de-identified and only be accessible to the PI, co-investigators, and VUIIS personnel. Scanning procedures may include: 1) Structural imaging, 2) Resting state functional imaging, 3) Functional imaging with task – while in the scanner, participants will complete one of two tasks:

1. **3-Probabilistic Reversal Learning Task:** In this task, we will show participants three decks of cards on the computer screen. Each deck will have a hidden probability of reward. Using the keyboard, they will select the deck of cards they think will earn them the greatest number of points. Participants will then receive feedback about the reward outcome for the deck they selected (+100 or -50 points). They are instructed to find the best deck, that will earn them the most points. However the best deck may change throughout the experiment. This task takes approximately 15-30 minutes to complete.

## **5.7 Randomization**

We propose an RCT with two treatment groups: Worry Intervention Training (WIT) and Befriending Therapy (called Connection Therapy during clinical trial). To produce balanced baseline characteristics, a computer program will be used to implement random assignment to treatment groups. To produce balanced sample sizes, desirable for statistical power and resource management reasons, the software uses existing group sizes to adjust the probability of assignment to particular groups. The PI will conduct the randomization procedures following the baseline assessment and will only tell the relevant interventionist which group the participant was assigned to. This will conceal allocation from assessors and coders.

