## **5.0 STUDY PROCEDURES**

---

This study has more than one part. We plan to complete these parts during either the same or different study visits. The different parts of the study are detailed below and include: answering questions about mental health symptoms, completing questionnaires, completing tasks on the computer, getting an MRI, and engaging in weekly 50-minute psychotherapy sessions over the course of 8-weeks. A single study visit is expected to last between 2 to 5 hours.

1. Screening and consent
2. Diagnostic Interview
3. Clinical Symptom Assessment
4. Cognitive Task Administration
5. Self-Report Rating Scales
6. MRI Scanning
7. Randomization
8. Treatment
9. Mid-treatment assessment (4-week)
10. End-of-treatment assessment (8-week)
11. Follow-up assessment

**5.1 Screening and Consent:** Subjects will be asked if they would like to participate in the current study. This screening will occur over the phone or in person using the Screening Form or Phone Screening Script. Informed consent will be obtained by study personnel directly involved in the research (i.e. research staff or the PI). Personnel have completed IRB training and have considerable experience running studies on psychiatric populations. Informed consent will be obtained in the research offices at the Psychiatric Neuroimaging

Program or over Zoom. A research staff member will explain the applicable procedures and the possible risks and benefits to the subjects. The details of the informed consent procedure are as follows:

1. The investigator or research staff and the subject will read together the entire consent form.
2. The subject will be asked details about the study. To document that the subject has read the consent form and has the capacity to understand the most important details, the investigator will use the appropriate Informed Consent Survey. The questions will be read by the investigator or research staff and the answers will be recorded. If the subject is unable to answer any of the questions, or if the subject demonstrates a lack of understanding, the investigator or research staff member will then review the details of the study again. Subjects who are unable to answer the questions, even after additional information is provided, will be excluded from the study.

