### **Reporting of Adverse Events (AEs) or Unanticipated Problems involving Risk to Participants or Others**

The PI and study personnel will review any AEs that occurred during a participant's study experience and determine their cause and severity. AEs rated as grade two or higher on the scale below will be reported to the IRB within 7 days of the receipt by the Investigator when the report identifies a new risk or a change in the risk-potential benefits profile. In conjunction with the IRB, the PI then will determine if modifications to the protocol are warranted. At the end of each year that this study continues, an annual report of AEs will be collected and shared with the IRB.

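### The PI runs an allocation that depends on running group sizes and may also take consent and oversee diagnosis, so the next arm is partly predictable to someone who can influence entry

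*Protocol*

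**What the plan says.** Protocol Section 5.7 sets out the allocation in four steps.

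- Random assignment is by computer: "To produce balanced baseline characteristics, a computer program will be used to implement random assignment to treatment groups".
- A second sentence gives a separate aim, "To produce balanced sample sizes, desirable for statistical power and resource management reasons", and the means: "the software uses existing group sizes to adjust the probability of assignment to particular groups". The probability function is not stated.
- The operator is named: "The PI will conduct the randomization procedures following the baseline assessment". The PI "will only tell the relevant interventionist which group the participant was assigned to".
- The protection claimed is: "This will conceal allocation from assessors and coders". People who screen or consent patients are not mentioned.

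Other sections give the same person a part in entry. Section 5.1 states: "Informed consent will be obtained by study personnel directly involved in the research (i.e. research staff or the PI"). Section 5.2 puts the research assistant who gives the diagnostic interview under the PI's supervision. Section 4.0 lists the PI as key personnel on three studies that feed recruitment. Section 6.0 (Intervention) has the PI supervise every study therapist for the duration of the trial.

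**The concern.** Allocation concealment means that whoever decides on a patient's entry cannot foresee the arm. Two features of this plan work against it. The probability of assignment leans on the current group sizes, so knowing the counts tells you something about the next draw. And the one person certain to know the counts, because that person has run every earlier draw, may also consent patients and oversees the diagnostic work that feeds eligibility.

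If entry decisions respond to the expected arm, even unconsciously, the groups can differ systematically in prognosis. Blinding the assessors does not prevent this. Adjustment for measured covariates does not reliably remove it, because the selection may rest on impressions that nobody recorded. The comparison of the worry intervention with befriending would then no longer be protected by randomisation.

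**Working it through.** **Inputs.** The goal is 30 randomised per group, 60 in all (Section 4.0, Planned Enrollment). The allocation uses existing group sizes (Section 5.7). The rule itself is not given, so the rules below are assumptions, shown as a range. The protocol states no figure for predictability, so there is none to reproduce.

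**Rules considered.**

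- Biased coin: when the groups are unequal, the smaller one is chosen with probability p; when equal, 1/2.
- Urn rule: the chance of an arm equals the share of past patients in the other arm.
- Simple randomisation, as reference.

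**Quantity.** The expected share of the 60 assignments guessed correctly by someone who knows the counts and always names the more likely arm. At each step this is max(P, 1 − P), averaged over the sequence (simulation, 40,000 replicates per rule).

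**Analytic check for the biased coin.** With r = p/(1 − p), the long-run value is 1/2 + (r − 1)/(4r).

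- p = 0.60: r = 1.5, so 0.5 + 0.5/6 = 0.583
- p = 2/3: r = 2, so 0.5 + 1/8 = 0.625
- p = 0.75: r = 3, so 0.5 + 2/12 = 0.667
- p = 0.80: r = 4, so 0.5 + 3/16 = 0.688
- p = 0.90: r = 9, so 0.5 + 8/36 = 0.722
- p = 1: odd-numbered draws are even chances and even-numbered draws are certain, so (0.5 + 1)/2 = 0.75

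| Rule | Simulated share correct, N = 60 | Expected correct of 60 |
|---|---|---|
| Simple randomisation | 0.500 | 30.0 |
| Urn | 0.555 | 33.3 |
| Biased coin, p = 0.60 | 0.580 | 34.8 |
| p = 2/3 | 0.622 | 37.3 |
| p = 0.75 | 0.665 | 39.9 |
| p = 0.80 | 0.686 | 41.1 |
| p = 0.90 | 0.721 | 43.3 |
| p = 1.0 (limit) | 0.750 | 45.0 |

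The simulated and long-run values agree to within 0.003. Every size-dependent rule exceeds 50%. The excess over 30 correct guesses runs from 3.3 (60 × 0.055) to 15 (60 × 0.25).

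**Where such knowledge could act.**

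- *Before or at consent.* The PI may take consent, and may be among the key personnel who invite patients from the feeder studies.
- *At eligibility.* Section 3.0 lets the diagnosis rest on a structured interview, a clinician's interview, record review, or a combination. The delusion conviction threshold is an interviewer's rating (Sections 3.0 and 5.3). Up to 150 people are to be enrolled so that 60 are randomised, so many who consent will not go on to randomisation.
- *Between baseline and randomisation.* Sections 5.7 and 5.8 place the draw after baseline but do not say that eligibility is closed first. The intent-to-treat set in Section 8.0 requires both a completed baseline and randomisation, so a patient held back at this point would not appear in it.

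**The case against.** The best defence is that assignment is computer-generated and drawn only after consent and baseline. Several entry criteria are numerical cut-offs (worry score at least 44, premorbid IQ above 79, conviction at least 3), which narrows discretion. The PI tells only the therapist, so research staff who take consent are not informed of past assignments. The PI is not named as an outcome rater. The size rule also does its stated job: at p = 2/3, group sizes fall within 28 to 32 in 97% of simulated trials, against 48% for simple randomisation.

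All of this stands and limits the exposure essentially to the PI, at the points where the PI acts on entry. It does not close the route, because nothing separates the PI from consent or from oversight of diagnosis. The PI's freedom over the timing of the draw is an inference from the absence of a lock; the text does not state it.

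A reader might go further in two directions that the protocol does not support.

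- *That the size rule contradicts the promised baseline balance.* Section 5.7 links baseline balance to random assignment, which does balance in expectation, and links the size rule only to sample sizes. Chance imbalance at 30 per group belongs to any unstratified trial of this size. Minimisation would be a design preference, and a change of algorithm part-way through has costs of its own.
- *That an unblinded PI alone decides on adverse events.* The adverse event section gives the task, to review events in a participant's "study experience and determine their cause and severity", to the PI together with study personnel. Adverse events are not an endpoint of either aim in Section 8.0. A supervisor of two different psychotherapies will know the arm in any case.

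**Conclusion.** The point holds as a weakness of allocation concealment. The protocol gives one person both knowledge of the running counts and a possible hand in entry, and its concealment statement leaves out those who screen or consent.

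Predictability is about 56% to 75%, against 50%. This assumes an urn or biased-coin rule and 60 patients. The top value is the limiting case in which the smaller group is always chosen; with p no higher than 0.90 the range ends at 72%. These figures measure opportunity. They do not estimate bias in the treatment effect, which the document gives no basis for computing. Nothing in the protocol indicates that selection has taken place.

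The change should be made, because this kind of bias cannot be removed afterwards and prevention is cheap.

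**What to change.** By amendment to Sections 5.1, 5.2 and 5.7, for all further patients:

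1. Record and lock eligibility and baseline data before the program is run.
2. Have an existing team member with no part in consent, eligibility or outcome rating run the program and pass the result only to the treating therapist.
3. Keep the PI out of consent and eligibility decisions. Merely hiding the running totals from the PI would not work, since the PI learns assignments by supervising the therapists.
4. State that the upcoming assignment is concealed from everyone who screens or consents, as well as from assessors and coders.

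The allocation algorithm need not change. The cost is a short amendment and some shifting of tasks within the present team. Because the protocol is version 1.5 of January 2023 and patients may already have been randomised, the change protects only those still to come.

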## **5.8 Treatment**

After the initial study visit, subjects will be randomly assigned to receive one of two types of psychotherapy with a qualified psychotherapist: Worry Intervention Training (WIT) or Befriending therapy (also referred to as "Connection Therapy" in the ICD to minimize expectancy bias. In both therapy conditions, subjects will meet with a psychotherapist for 6, 50-minute sessions over the course of 8 weeks. In WIT, they will speak with the

therapist about the impact of worry on their daily life. The therapist will offer tools for managing those worries that they can practice at home, in order to free up their headspace to focus on things that are important to them. In Befriending Therapy, therapy sessions will focus on taking time off from thinking about life's difficulties by connecting with your therapist around topics that interest you. Both types of therapy have been shown in research trials to make people feel safer, happier, and more motivated to do the things they want to do.

### **5.9 Mid-Treatment Assessment**

In the middle of treatment (Week 4) study participants will be asked to complete a brief, 2-3 hour assessment. This assessment will include clinical interview, self-reports, and the 3PRL task (described above).

### **5.10 End of Treatment Assessment**

At the end of treatment (Week 8), all assessments (except the diagnostic interview and childhood trauma questionnaire), as well as the MRI, will be repeated.

### **5.11 24-Week Follow-up**

At week 24, research subjects will be invited to complete a follow-up visit. This visit will be 2-3 hours and focus on clinical interview, self-report, and select cognitive tasks

## **6.0 RISKS**

---

The following procedures may have risks: clinical assessments, neuropsychological and cognitive testing, MRI scanning, psychotherapy intervention.

**Confidentiality:** The risk of confidentiality will be minimized by thorough training of all research personnel and the high level of security in our information systems. All subjects will be assigned a Subject ID numerical code to maintain anonymity of the participants and their test results. The Subject ID will serve as the primary identifying information on research data forms. Research personnel will comply with the ethical standards set forth by the IRB, NIH and the American Psychological Association. The records of this study, to include paper records and electronic records, will be kept private and secured in locked filing cabinets or in password-protected databases (RedCap) and folders (for videos). In any published report, we will not include any information that will make it possible to identify a subject.

If at any point during the study sessions the participant expresses any intent to harm themselves or others or a researcher becomes concerned for their safety, the researcher will contact the primary investigator or another licensed clinical psychologist on the research team. The clinical psychologist will conduct the brief ASQ suicide risk screen and the Columbia suicide severity scale for the past month. If the clinician is concerned for the participant's immediate safety they will continue with a safety plan and provide mental health resources and discuss alerting a family member or loved one of the concerns. If the participant cannot contract for safety and the clinical psychologist believes they may be a threat to themselves or others then the participant would be brought to the Psychiatric Assessment Services (PAS) for an evaluation for inpatient admission. If the study visit is occurring over zoom and an individual cannot contract for safety, the clinical psychologist will call 911 to the individual's address. Participants will be informed of this procedure during the informed consent process and again at the start of therapy.

**Clinical Assessments:** The risk of the clinical assessments involves the possibility that participants might be asked questions that cause them distress. These would be questions consistent with any diagnostic and clinical evaluation. In order to address this risk, participants will be told they can decline to answer any questions and can stop the evaluation at any time. Participants may also feel fatigued, bored or frustrated by the length of the clinical assessments. Participants will be allowed to take breaks at any time and assessments can be completed across multiple sessions if needed.

**Cognitive Testing:** The risk of neuropsychological and cognitive testing involves the possibility that participants may experience mental fatigue or anxiety. The nature of the tests and that the data are for research purposes only will be described to study participants. Any neuropsychological tests that elicit excessive anxiety will be skipped. Subjects will be informed beforehand that they may take a break at any point during administration of neuropsychological tests and cognitive paradigms.

**MRI:** With respect to MRI scanning, there are no known health risks associated with the magnetic field produced by 3.0T scanners in healthy subjects. The FDA has indicated that they consider MR imaging on machines up to 4.0T to pose no risk. Activation studies with fMRI are routine, and are in place in a number of institutions in the U.S. and around the world. There may be minor discomforts for subjects because they must lie motionless for an extended period of time. Physical discomfort will be minimized with cushions and foam used to hold the head without placing undue pressure on it. Subjects are allowed to dress comfortably, and they are covered with a light cotton cover to keep them warm. Participants must wear hearing protection. Persons at primary risk from exposure to the magnet include persons with metal surgical implants, and anyone with implanted electric/magnetic devices (e.g. a pacemaker, orthodontic braces, aneurism clips, IUDs). Such individuals will be excluded from the imaging portion of the study. People at secondary risk will also be excluded from the imaging portion of the study. These include people with significant chronic physical illnesses (e.g. asthma, heart conditions, diabetes, hemophilia) or neurological disorders (e.g. epilepsy, autism, or other syndromes). To ensure that no such subjects in these risk groups are included in the study, subjects must fill out a screening that is reviewed by the MRI operator prior to scanning (see attached documents). There is a risk that some subjects may be anxious (claustrophobic) about lying in an enclosed space. We anticipate that the occurrence of such responses will be minimal given that subjects are told about the MRI scanning procedures and that they will be placed in a hollow tube-like scanner beforehand during the consent process. Moreover, subjects will be able to stop the session at any time, by pressing a switch held in one hand. The switch activates a loud buzzer in the control room. There is also an intercom voice link with the control room that allows verbal communication between subject and experimenters. All study personnel who have contact with participants in the scanner are trained in the above described risks and procedures to avoid risk. In the highly unlikely event of an adverse event occurring during scanning, a Radiology resident is on-call at all times to render assistance if necessary. This person can be reached by calling the Medical Center Operator at [name] and asking them to page the Radiology resident on call ([name]).

As a consequence of the scanning procedure an abnormality might be detected in a subject's brain. In the event that the MRI technologist suspects there may be an abnormality, we will have the technician on duty burn a CD containing DICOM images of the subject. The RA running that participant through the study will take that disc to the radiology department in Medical Center North and leave it with [name] assistant. [name] is a neuroradiologist who has agreed to look at our incidental findings. [name] will send [name] an email to confirm the disc was received, and [name] will confirm any findings. If the neuroradiologist finds the abnormality requires attention, the PI will contact the subjects via phone as soon as possible. On the phone call we will provide the subject with this information, and help them identify referrals as needed.(see the Communicating\_Incidental\_Findings document for a template of a phone call)

**Intervention:** The intervention will be conducted in a safe, supportive clinical environment implemented by trained psychotherapists employed at Vanderbilt University Medical Center. Intervention procedures (i.e. the delivery of WIT or Befriending therapy) will mirror procedures regularly conducted in the Vanderbilt Adult Psychiatry Outpatient Clinic (VAPOC), including review of confidentiality and its limits and the use of either Zoom teletherapy or private, dedicated clinical offices. Notes from the intervention sessions will not be included in the participant's medical record and will not be directly shared with their other providers except in the case of imminent safety risk. Notes about the therapy sessions will be anonymized and kept in encrypted files on a password-protected server. Video recordings will also be kept on password protected servers that is only accessible to the research staff and will not include any identifying information.

The intervention, particularly the WIT intervention, is designed to address distress and preoccupation surrounding persecutory delusions. Discussion of these topics may be upsetting to some participants. However, all therapists in the trial will have at least 3 years of experience working with individuals with psychotic disorders and will be fully trained in the WIT intervention by experts in the field. The PI is a licensed clinical psychologist with over a decade of experience working with individuals with psychosis, and the PI will be providing supervision and support for all therapists throughout the trial, in order to help manage issues that arise during therapy. Furthermore, during the screening process, participants will be informed that one of the therapies is designed to address feelings of worry about others harming them, and that these topics will be addressed in therapy. They will be reminded throughout the screening and consent process that the research study includes therapy sessions with a professional therapist, and will be asked whether this is something they want to engage in. Distress during or between sessions will be monitored by the participant's study therapist and the intervention will be adjusted to minimize distress. For instance, if a participant is distressed by conversation about a specific topic, the therapist will discuss with the participant if they would like to change the topic and may conduct a grounding or breathing exercise to reduce distress in session. Therapists may check in with participants throughout the week depending on the participant's preference.

Befriending therapy involves discussion of neutral topics that interest the participant, such as sports or music and is specifically not focused on the individual's illness or symptoms. Befriending therapy allows for a development of a therapeutic alliance, and therefore some individuals experience loss of that support after therapy ends. The therapist will work with each participant to address this potential loss and will refer them to additional therapy services after the 8 weeks, if requested.

